## Assignment of interventions: blinding

### Who will be blinded {17a}

Data analysts and statisticians will be blinded.

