### Eligibility criteria {10}

Inclusion criteria
Histologically proven locally advanced SCCHNIndication for radiotherapy or radio-chemotherapyPossession of and ability to use a smartphoneAge ≥ 18 yearsWritten informed consentCapacity of the patient to contract

Exclusion criteria
Nasopharynx cancerPregnancy, lactationTreatment with epidermal growth factor receptor antibodies (given or planned)Expected noncompliance

Radiation dermatitis and oral mucositis will be assessed by two independent observers (specially trained nurses, technicians, or physicians) weekly during the period of radiotherapy, at 60 Gy and at end of treatment (EOT). If the graduation varies between the two observers, toxicities will be assessed by an additional observer. Observers are required to be very experienced in rating toxicities and will additionally undergo a particular briefing prior to the start of this study.

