### Intervention description {11a}

#### Standard skin care

In both the experimental (A) and the control arm (B), standard skin care is to be performed by the patient from the beginning of radiotherapy. Standard skin care may vary at the participating centers. At the University of Lübeck, it includes fatty cream with 2–5% urea (fatty cream alone, if patients do not tolerate urea) and mometasone furoate cream. The treatment will be continued until 1 week after EOT or until a patient experiences grade ≥ 2 moist desquamation or grade ≥ 3 radiation dermatitis.

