#### Reminder app

The patients in the experimental arm (Arm A) are supported by a reminder app (“CareReminder”), which has been developed by the professional company Nextlabel OHG from Lübeck, Germany. This app will remind the patients four times a day to perform skin and mouth care. Instructions are given how to perform it properly. The patients may postpone each required care procedure for up to 2 hours. Finally, the patients are asked to state for each procedure whether or not they performed it. To increase the patients’ motivation, they will earn points for each successfully performed procedure.

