### Outcomes {12}

Primary endpoint is the rate of grade ≥ 2 radiation dermatitis Common Terminology Criteria for Adverse Events (CTCAE v5.0) at 60 Gy of radiotherapy, the minimum planned total dose for all patients receiving definitive or adjuvant radiotherapy for locally advanced head and neck cancer. In addition, the following endpoints will be evaluated:
Radiation dermatitis grade ≥ 2 at EOTRadiation dermatitis grade ≥ 3 at 60 Gy and at EOTRadiation-induced oral mucositis grade ≥ 2 at 60 Gy and at EOTRadiation-induced oral mucositis grade ≥ 3 at 60 Gy and at EOTQuality of lifePain

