### Composition of the data monitoring committee, its role and reporting structure {21a}

A data monitoring committee is not needed, since all patients participating in this trial receive the same anticancer treatment, the same number and type of visits, and the same treatment for radiation dermatitis, oral mucositis and other toxicities as they would have received if not participating in the trial.

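### The observers who grade the primary endpoint are not among those blinded, although the arms differ only by a smartphone app and masking appears feasible

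*Protocol article*

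**What the plan says.** The section on who will be blinded (item 17a) consists of one sentence: "Data analysts and statisticians will be blinded".

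The observers are described under the eligibility criteria (item 10) and again under the plans for outcome assessment (item 18a). Dermatitis and oral mucositis "will be assessed by two independent observers (specially trained nurses, technicians, or physicians"), every week, at 60 Gy and at the end of radiotherapy. On disagreement the rule is: "If the graduation varies between the two observers, toxicities will be assessed by an additional observer". Observers must be very experienced and receive a briefing before the study. Neither section mentions masking to the arm.

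The endpoint they determine is defined under Outcomes (item 12): "Primary endpoint is the rate of grade ≥ 2 radiation dermatitis Common Terminology Criteria for Adverse Events (CTCAE v5.0) at 60 Gy of radiotherapy".

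On what separates the arms, the intervention section says of Arm A: "This app will remind the patients four times a day to perform skin and mouth care". Skin care is common to both: "In both the experimental (A) and the control arm (B), standard skin care is to be performed by the patient from the beginning of radiotherapy". Mouth care is likewise standard in both arms. In explaining why no data monitoring committee is needed (item 21a), the protocol adds that participants receive "the same number and type of visits, and the same treatment for radiation dermatitis, oral mucositis and other toxicities" as they would outside the trial.

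**The concern.** Whether a patient counts as an event depends on which side of the grade 1/2 boundary an observer places the skin reaction. The protocol itself expects raters to differ, since it provides a third one. Its background and discussion also set out the expectation that reminders lower dermatitis rates. An observer who is aware of the arm could therefore lean, without intent, towards the lower grade in Arm A.

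Such a lean would be fixed in the data at the moment of grading, and blinding the analysts cannot remove it later. In the primary comparison it would look like a benefit of the app. Nothing keeps the roles apart either: physicians may be observers, and under Implementation (item 16c) investigator physicians enrol patients and assign them to arms.

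**Working it through.** **Inputs from the protocol (Sample size, item 14).** Chi-square test, two-sided 5%, grade ≥ 2 dermatitis in 85% under standard care alone, a reduction by 20% (read as 85% to 65%), 80% power, 80 patients per arm in the full analysis set.

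**The plan's own figure.** Power is the sum, over all pairs of event counts (x_B, x_A), of Bin(x_B; 80, p_B) × Bin(x_A; 80, p_A) for the pairs in which the test rejects. With p_B = 0.85 and p_A = 0.65 this gives:

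| Test | Power at 80 per arm |
|---|---|
| Fisher's exact | 79.9% |
| Continuity-corrected chi-square | 79.5% |
| Uncorrected chi-square | 84.8% |

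So 80 per arm agrees with 80% power under Fisher's exact or the corrected test. Masking the observers changes neither this figure nor the 168 to be randomized.

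**Illustration of biased grading.** The same sum is used with no true effect: the true rate is 85% in both arms, but Arm A is recorded at 0.85 − s. The shift s is an assumption; the documents give no value for it.

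| Assumed shift s | Recorded rate in Arm A | Expected patients out of 80 | Uncorrected chi-square | Corrected chi-square | Fisher's exact |
|---|---|---|---|---|---|
| 0 points | 85% | 0 | 4.8% | 2.8% | 3.0% |
| 5 points | 80% | 0.05 × 80 = 4 | 13.0% | 8.9% | 9.4% |
| 8 points | 77% | 0.08 × 80 = 6.4 | 25.1% | 18.7% | 19.6% |
| 10 points | 75% | 0.10 × 80 = 8 | 35.5% | 27.8% | 28.9% |

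For shifts of 5 points or more, nearly all of these rejections favour Arm A (12.7 of the 13.0 percentage points at s = 5 with the uncorrected test). The item 14 calculation and the statistical methods (item 20a) both name the chi-square test, and item 20a replaces it by Fisher's exact test only when an expected cell count falls below five. The uncorrected column is therefore a fair reading of the plan, and the other two columns show how far the result depends on the test.

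**What masking would and would not do.** Masked observers still make errors, but these should not depend on the arm. With sensitivity and specificity both 0.95 in each arm (assumed), the recorded rate under no effect is 0.85 × 0.95 + 0.15 × 0.05 = 0.815 in both arms, and the false-positive rate of the uncorrected test is 5.0%. Power for 85% versus 65% falls from 84.8% to 73.6%. Masking thus protects the error rate. Experience, briefing and double rating are what protect power.

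**Is masking feasible?** The documents name one difference between the arms, the app on the patient's own phone. Skin care and mouth care are standard in both arms, so no product applied to the skin or mouth is specified for one arm only. The protocol gives no reason for leaving the observers unmasked.

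**The case against.** The strongest case on the other side has four parts.

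1. *The protocol does not say that observers know the arm.* This is correct. A reader might infer it from item 17a, but the text only leaves them off the list of those blinded, and some may in practice be unaware. The point is that the protocol does not provide for their being unaware.

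2. *Safeguards exist.* Two independent, experienced and briefed raters use published criteria, and a third resolves differences, so a shift would have to survive agreement or adjudication. This makes large shifts less likely and deserves credit. It does not remove a lean that all raters share, and in context independent most naturally means independent of each other.

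3. *Masking may not last.* The app prompts four times a day, patients are seen at least five days a week for six to seven weeks, and the interim analyses (item 21b) use a dissatisfaction rate, so someone presumably asks patients about the app. A reader might infer that the app leaves no trace an observer could notice; the documents do not show that. Imperfect masking still lowers the risk, and recorded breaches let it be judged.

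4. *The rates are hypothetical.* This also stands. Nothing in the documents supports a particular shift, and the rates depend on the test.

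**Conclusion.** The concern holds as an avoidable risk of detection bias on the primary endpoint and on the mucositis endpoints. Followed as written, the plan masks the analysts and makes no provision for masking those who decide the grade, in a trial where masking them appears feasible.

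The size is illustrative. If Arm A were under-graded by 5 to 10 points, the false-positive rate would be about 13% to 35% with the uncorrected chi-square test, or about 9% to 29% with Fisher's exact or the corrected test. These figures assume no true effect, an 85% true rate, 80 patients per arm and a shift confined to Arm A.

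A reader might go further and conclude that the superiority test is invalid. The documents do not support that: the error rate is inflated only if grading actually differs by arm, and nothing shows that it will. Blinding the analysts is not a fault either; it simply does not address this risk. The change is worth making because the possible bias concerns the primary endpoint and the remedy is small.

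**What to change.** State in items 10, 17a and 18a that:

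- both observers and the third, tie-breaking observer are kept unaware of allocation;
- they are chosen from existing trained staff who have no part in that patient's randomization, app instruction or app-satisfaction query;
- they do not see app data;
- patients are asked not to mention the app at assessments;
- any unblinding of an observer is recorded.

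If a site cannot arrange this with its existing staff, the protocol should say so, and the data should record whether its observers were masked.

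**Cost.** Sample size, visits, endpoints and treatment do not change. The downsides are rota constraints, mainly at the private practice listed under Study setting (item 9), and occasional disclosure by patients. That no extra staff are needed is an assumption, since the protocol gives no staffing figures. Patients cannot be blinded to the app, so pain and quality of life remain open-label after this change.

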### Procedure for unblinding if needed {17b}

Not applicable.

## Data collection and management

### Plans for assessment and collection of outcomes {18a}

The following parameters will be recorded prior to radiotherapy: Demographics, medical history, concomitant diseases, physical examination, performance status, primary tumor site, stage and histology, upfront surgery, planned chemotherapy, status of skin and oral mucosa, pain, and quality of life.

The following parameters will be assessed throughout the course of the trial:
Radiation dermatitis: assessed by two observers weekly during radiotherapy, at 60 Gy and at EOT according to CTCAE v5.0 [9]. If graduation varies, a third observer will be involved.Oral mucositis: assessed by two observers weekly during radiotherapy, at 60 Gy and at EOT according to RTOG criteria [10–13]. If graduation varies, a third observer will be involved.Quality of life: assessed prior to radiotherapy, at 60 Gy and at EOT with European Organisation for Research and Treatment of Cancer (EORTC) Quality of Life Questionnaire (QLQ)-C30 Version 3.0 and EORTC QLQ-H&N35.Pain (within radiation fields): assessed prior to radiotherapy, weekly during radiotherapy, at 60 Gy and at EOT with a visual analog scale (from 0 = no to 10 = maximum pain).Other adverse events will be assessed on an ongoing basis according to CTCAE v5.0 [9].

The timeline of the study procedures including the assessments is given in Fig. 1.

**Fig. 1 Fig1:**
[figure not shown]
Schedule of enrolment, interventions and assessments. **RT* radiotherapy

### Plans to promote participant retention and complete follow-up {18b}

The last day of radiotherapy (EOT) is also the end of the follow-up period. Patients are seen at least 5 days per week by medical staff members. Thus, it is unlikely that patients will be lost to follow-up. If patients withdraw their consent to participate in the trial or die during the course of radiotherapy, the data available until this point in time will be used for analyses.

### Data management {19}

#### Patient identification list

All data relating to patients will be recorded in a pseudonymous way. Each patient will be identifiable only by the unique patient number, date of birth and sex. A patient identification list will only be kept in the relevant trial centers and will not be forwarded to the sponsor.

#### Documentation sheet

Data collection will be done using the data documentation sheets**.**

The data documentation sheets must be filled in using a ballpoint pen. Fountain pens or pencils may not be used. Corrections must be made as follows: cross the error out once with a straight line, enter the correct information next to it and note the date and/or reason for correction. Comments must be made if data fields cannot be filled in because of missing information.

The sheets should be filled in as soon as possible and should be submitted to the checker for review, signed, dated and forwarded to the trial management. All data will be pseudonymized before they are forwarded for analysis. The data will be handled according to the General Data Protection Regulation (GDPR). The data will be brought into one database and analyzed in accordance with a predefined statistical analysis plan. At this stage, subgroup analyses are not planned. At each interim analysis, the need for subgroup analyses will be re-evaluated.

#### Storage of trial documents

The originals of all key trial documents, including the documentation sheets, will be kept at the trial headquarters (i.e., the sponsor responsible for the trial) for a minimum of 10 years after the final report.

The principal investigator/head of the trial center will keep all administrative documents (written correspondence with the ethics committee, regulatory authorities, trial management, trial headquarters), patient identification list, signed informed consent forms, copies of the documentation sheets and general trial documentation (protocol, amendments) for the abovementioned period. Original patient data (patient files) must also be kept for the length of time stipulated for the trial centers, but not for less than 10 years.

### Confidentiality {27}

Data will be collected in accordance with the regulations set out in the Data Protection Act. All findings from the clinical trial will be stored on electronic data storage devices and treated with utmost confidentiality. Organization measures have been taken in order to prevent the data from being communicated to unauthorized persons. Patients will only be identified via their individual patient numbers throughout the entire documentation and evaluation phase and their full name will not be used.

### Plans for collection, laboratory evaluation, and storage of biological specimens for genetic or molecular analysis in this trial/future use {33}

Not applicable.

## Statistical methods

### Statistical methods for primary and secondary outcomes {20a}

All data recorded in the case report forms describing the study population, toxicity and quality of life will be analyzed descriptively. Categorical data will be presented in contingency tables with frequencies and percentages. Continuous data will be summarized with at least the following: frequency (n), median, quartiles, mean, standard deviation (standard error), minimum and maximum. Number of patients with protocol deviations during the study and listings describing the deviations will be provided. In general, chi-square tests will be used to compare percentages in a two-by-two contingency table, replaced by Fisher exact test if the expected frequency in at least one cell of the associated table is less than five. Stratified two-by-two contingency tables will be analyzed using Cochran-Mantel-Haenszel tests. Logistic regression models serve as multivariable methods for binary endpoint data. Comparison of ordinal variables between treatment arms will be performed using the asymptotic Wilcoxon-Mann-Whitney test, replaced by its exact version in case of ordinal categories with small number of categories and/or sparse data within categories. Any shift in location of quantitative variables between study groups will be performed with the Wilcoxon-Mann-Whitney tests as well. Time-to-event data will be analyzed by Kaplan-Meier methods, when merely non-informative censoring occurs. For statistical comparison, the log rank-test will be provided supplemented by multivariate Cox proportional hazards models. The data analysis will be performed according to the statistical analysis plan, and which will be finalized prior to database lock and prior to any statistical analysis.

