### Sample size {14}

This study aims to show that standard skin care supported by a reminder app is superior to standard skin care alone regarding the avoidance of grade ≥ 2 dermatitis up to 60 Gy in patients irradiated for locally advanced head-and-neck cancers.

The null hypothesis of equal grade ≥ 2 dermatitis rates in both groups is tested against the two-sided alternative hypothesis of unequal dermatitis rates. The calculation of the sample size considered the following assumptions:
Application of a chi-square testTwo-sided significance level of 5%Rates of grade ≥ 2 dermatitis of 86–92% with standard care alone according to previous studiesAssumption of a grade ≥ 2 dermatitis rate of 85% in the standard care alone group (“worst-case”)Clinical importance of the impact of the reminder app = reduction of grade ≥ 2 dermatitis by 20%Statistical power of 80%

When considering these assumptions, 80 patients are needed per arm within the full analysis set. Assuming that 5% of the recruited patients will not qualify for the full analysis set, 168 patients need to be randomized.

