## Assignment of interventions: allocation

### Sequence generation {16a}

The patients will be assigned two code numbers: the number of the contributing center plus a patient identity number, continuously ascending, starting with 001.

After registration, patients will be randomized in a 1:1 ratio to receive either standard care supported by a reminder app (Arm A) or standard care (Arm B) for treatment of radiation-related skin toxicity.

A stratified block randomization will be performed. Stratification will be done using the following prognostic factors:
Tumor site: oropharynx/oral cavity versus hypopharynx/larynx.Treatment approach: radio-chemotherapy versus radiotherapy alone.Participating site.

The randomization will be performed centrally at the ‘Zentrum für Klinische Studien’ (ZKS) at the University of Lübeck, Germany via fax. The proceeding is based on standard operating procedures (SOPs) of the ZKS. The fax document has to be completed and finally be signed and dated by the investigator. Once the randomization is allocated to the patient it cannot be changed.

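### Randomization is stratified by three prognostic factors, but the only test linked to the primary hypothesis is an unstratified chi-square; name one stratified primary test, and use the baseline pain and quality-of-life values

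*Protocol article*

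**What the plan says.** **Design.** Under Sequence generation {16a}, patients are randomized 1:1 in stratified blocks. "Stratification will be done using the following prognostic factors": tumor site (two levels), treatment approach (two levels) and participating site. Study setting {9} lists four sites. Intervention description {11a} adds that standard skin care may vary between centers.

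**Primary comparison.** Outcomes {12}: "Primary endpoint is the rate of grade ≥ 2 radiation dermatitis", graded by CTCAE at 60 Gy. Sample size {14} states the null hypothesis of equal rates and then lists a chi-square test, a two-sided 5% level, 80% power and a control rate of 85% as assumptions. No stratification is mentioned there. The result is that "80 patients are needed per arm within the full analysis set".

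**Methods section.** Statistical methods {20a} gives a rule by type of data: "In general, chi-square tests will be used to compare percentages in a two-by-two contingency table", with Fisher's exact test for small expected counts. The next sentences name CMH tests for stratified tables and logistic regression for binary endpoints. Neither is given an endpoint, strata or covariates.

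**Pain and quality of life.** For quantitative outcomes the same section says: "Any shift in location of quantitative variables between study groups will be performed with the Wilcoxon-Mann-Whitney tests as well". Plans for assessment {18a} collects baseline values: "Quality of life: assessed prior to radiotherapy, at 60 Gy and at EOT". Pain is also scored before radiotherapy, on a 0 to 10 scale. The section describes no use of these baseline values.

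**The concern.** A trial that balances on factors it calls prognostic would normally use them in the primary analysis. Stratified blocks remove most of the between-stratum variation from the difference between arms. The standard error of an unstratified chi-square still contains that variation. If the factors do predict dermatitis, the test rejects too rarely under the null hypothesis and gives up some power.

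Three methods for binary data are named and none is designated as the lead. The reader cannot tell from the protocol which p-value will decide the trial.

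For pain and quality of life, a two-sample comparison that makes no use of the pre-treatment value gives up precision that the collected data could supply.

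**Working it through.** **1. Inputs from the protocol.** Control rate 85%; reduction by 20%, read here as 20 percentage points (to 65%); two-sided 5%; 80% power; 80 per arm; 1:1 allocation; strata 2 × 2 × 4 sites = 16, so 160/16 = 10 patients per stratum on average.

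**Assumptions.** The protocol gives no block size, no size of the prognostic effects and no baseline correlations. I took blocks of 4. Stratum effects were normal on the log-odds scale, with the standard deviations (SD) shown below.

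**2. The plan's own figure.** Uncorrected chi-square, pooled rate 0.75:

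n = [1.960·√(2·0.75·0.25) + 0.842·√(0.85·0.15 + 0.65·0.35)]² / 0.20² = (1.200 + 0.501)² / 0.04 ≈ 72.4, so 73 per arm.

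The continuity-corrected formula gives 83 per arm. At 80 per arm the power is:
- uncorrected chi-square: 83.8% by formula, 84.8% by exact enumeration;
- Yates-corrected chi-square: 79.5% exact;
- Fisher's test: 79.9% exact.

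So 80 per arm fits a corrected or exact unstratified test at 85% versus 65%. The total of 168 agrees with 160 × 1.05 = 168 (160/0.95 = 168.4).

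**3. Why the chi-square can be conservative.** Its variance uses p(1 − p) for the pooled rate p, which equals the mean of p_k(1 − p_k) over strata plus the variance of p_k between strata. Stratified blocks largely remove the second term from the true variance of the difference. CMH also leaves it out of the estimated variance:

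CMH = [Σ(a_k − n_Ak·m_k/n_k)]² / Σ[n_Ak·n_Bk·m_k(n_k − m_k) / (n_k²(n_k − 1))]

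where k is the stratum, a_k the events in Arm A, m_k all events, n_Ak and n_Bk the arm sizes, and n_k their sum.

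**4. Size of the effect.** N = 160, 85% versus 65%, 5,000 simulated trials per setting; Monte Carlo error is about 0.3 points for type I error and 0.5 for power. Both tests are uncorrected. Each cell shows chi-square / CMH.

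| Strata | SD (log-odds) | Type I error | Power | Change in power |
|---|---|---|---|---|
| 16 | 0 | 4.6% / 4.5% | 84.6% / 83.7% | -0.9 |
| 16 | 0.5 | 4.4% / 4.5% | 84.7% / 84.7% | 0.0 |
| 16 | 1.0 | 4.0% / 4.7% | 85.7% / 88.2% | +2.5 |
| 4 (site left out) | 0 | 5.3% / 5.2% | 84.7% / 84.4% | -0.3 |
| 4 | 0.5 | 4.6% / 4.8% | 85.4% / 86.0% | +0.6 |
| 4 | 1.0 | 4.4% / 5.1% | 84.7% / 87.1% | +2.4 |

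A further set with 16 strata and 3,000 trials per setting gave power of 85.9% / 87.6% at SD 0.8 and 86.3% / 89.6% at SD 1.2. The type I errors were 3.3% / 4.0% and 3.5% / 5.1%.

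**5. Baseline pain and quality of life.** With correlation r between baseline and later value, linear adjustment leaves a share 1 − r² of the variance:
- r = 0.3: 1 − 0.09 = 91%
- r = 0.5: 1 − 0.25 = 75%
- r = 0.7: 1 − 0.49 = 51%

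This compares adjusted with unadjusted means. It is only a guide to the gain over a rank test.

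**The case against.** **The chi-square may not be the planned primary analysis.** It appears as a sample-size assumption and as a general rule, and planning on an unstratified test does not exclude a stratified analysis. CMH and logistic regression are named in the sentences that follow. Lead test, strata and covariates are commonly left to the SAP, which is not shown. This stands in part: the protocol does not rule out a stratified primary test. It still ties only the unstratified test to the hypothesis.

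**The p-value could be picked afterwards.** A reader might infer this from the three methods named. The protocol does not support it: the SAP is to be final before database lock and before any analysis, and data analysts and statisticians are blinded.

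**Baseline is ignored.** A reader might infer this from the Wilcoxon sentence. It does not say whether raw values or changes are compared, and a Wilcoxon test on changes is not excluded. An unadjusted comparison of randomized arms is also valid. What stands is that no use of baseline is described.

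**The remedy has a cost.** With 10 patients per stratum, each arm has about 5, and 15% of 5 is 0.75 expected control patients without the event. Many strata will be sparse. The 16-stratum simulations include this sparseness, and CMH kept its level (4.5% to 4.7% in the table), but a pooling rule is needed.

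**Conclusion.** The point holds as a modest, nearly free improvement. The protocol should name one primary test that respects its own stratification. On the 85% versus 65% reading, CMH in place of the chi-square changes power by about -1 to +3 points. The upper end needs strongly prognostic strata (SD about 1.0 to 1.2 on the log-odds), which is an assumption.

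Two stronger readings are not supported:
- **The test is invalid.** The chi-square's type I error was 3.3% to 5.3% across the settings shown, which is no clear inflation.
- **The trial is too small.** With 80 per arm, CMH power was at least 83.7% in every setting simulated at 85% versus 65%. A larger CMH gain (74.9% to 79.7% at SD 1.2) appears if the 20% is read as relative, 85% to 68%. On that reading the plain formula needs 97 per arm, and 80 give about 72% power, so the stated sample size fits only the absolute reading.

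The pain and quality-of-life part holds only as a proposal to use data already collected. Its gain depends on correlations that the protocol does not give.

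**What to change.** **Primary endpoint.** In Statistical methods {20a}, and in the SAP, state that the primary test is the CMH test stratified by the randomization factors. Report a stratified risk difference with its 95% CI. Fix in advance, without reference to outcome by arm, how sparse strata or small sites are pooled. Keep the unstratified chi-square as a sensitivity analysis and give logistic regression a stated supportive role.

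**Pain and quality of life.** State that these outcomes at 60 Gy and EOT are compared with adjustment for the pre-radiotherapy value, for example by ANCOVA or a mixed model that also includes the stratification factors. The Wilcoxon test can remain as a sensitivity analysis, given the bounded scales.

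**Cost.** Wording only; no new data and no change in sample size. The downside is about 1 point of power on the primary test if the factors turn out not to be prognostic.
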